#### Primary outcomes

The study’s primary outcomes (Table 4) are reductions in intimate violence, violence against children, increased father-child engagement (early stimulation), and improvements in early childhood development outcomes.

**Table 4 Tab4:** Summary of primary outcome measures

Primary outcome	Measure description	Questionnaire
Intimate partner violence (IPV): Perpetration and Victimization	Proportion of young fathers and their wives reporting perpetrating or being a victim of physical, sexual, and/or emotional IPV in the past three months. Assessed via six measures: insulted; shouted or yelled; slapped; pushed or shoved; threw something at that could hurt; physically forced unwanted sex	Male and Female caregiver
Harsh violent discipline of children	Proportion of fathers reporting they used a form of harsh/violent discipline with their child in the past month. Items include the following: shook child; shouted, yelled at, or screamed at child; spanked, hit, or slapped child on the bottom with bare hand; hit child on the bottom or elsewhere on the body with something like a belt, stick, or other hard object; hit or slapped child on the face, head, or ear; hit or slapped child on the hand, arm, or leg; beat child up, that is, hit him/her over and over as hard as you could	Male
Fathers’ increased use of child engagement (early stimulation) activities	Proportion of fathers reporting use of early learning and play activities with child (i.e., stimulation activities). Activities include the following: reading, telling stories, singing songs, taking child outside of the home, naming/counting things together, drawing things together, playing with a toy or object	Male
Early childhood development	Scores on the short-form version of the Caregiver Reported Early Development Instruments (CREDI) [46]	Male and Female

#### Secondary outcomes

The secondary outcomes (Table 5) include hypothesized antecedents to the primary outcomes with respect to knowledge, attitudes, and behaviors: improved couple communication, increased father engagement in household duties; improved father knowledge and attitudes regarding positive discipline; increased father use of positive discipline; and increased father engagement in health-promoting activities for children. In addition, norms measures are included to assess supportive normative social environments for father engagement and positive parenting, and family planning knowledge and behaviors are included to understand potential connections between father engagement, couple communication, and use of contraceptives.

**Table 5 Tab5:** Summary of secondary outcome measures

Secondary outcome	Measure description	Questionnaire
Couple communication and conflict resolution	Proportion of fathers and mothers reporting increased and improved communication with the other. Questions include the following: past month took time to listen to partner’s concerns; communicated with each other about things that frustrated you; talked about things that affect each other and the family; and asked questions and got feedback/input from each other before making final decisions; resolved conflicts/arguments amicably without physically hurting each other	Male and Female
Father engagement in household duties	Proportion of fathers who engage with household chores and caretaking activities in past three months. Items include the following: washed clothes; prepared food; bought food; cooked or fixed food for your child; dressed or changed the clothes of the child; gave your child a bath	Male
Father alcohol and drug use	Reduction in proportion of fathers’ heavy alcohol use (i.e., three or more drinks in a single day)	Male
Fathers’ use of emotional engagement towards child	Proportion of fathers reporting increased emotional engagement and affection towards children. Activities include the following: interact in a calm/gentle manner, use affirming language, recognize when they need to be comforted, use words of endearment, show approval, ask questions to engage with the child	Male
Fathers'knowledge of positive parenting and discipline skills	Proportion of fathers who can correctly distinguish between positive and harsh discipline. The list of discipline behaviors included in the survey as true/false questions are as follows: Taking a deep breath (calming yourself) when the child does something wrong before responding; Threaten to hit child; Tell your wife to take care of the child; Put child somewhere by him/herself; Redirect child's attention or behavior; Ask your wife for advice or help; Shout at child	Male
Fathers'attitudes towards positive parenting and discipline	Proportion of fathers who hold positive attitudes for the use of non-violent parenting practices. Items include the following: Stubborn children need to be hit to teach them right from wrong [reverse-coded].; A parent should never spank or hit a child.; Being violent with my child(ren) is not the only way to be an effective head of the family.; If a child is old enough to defy a parent, then he/she is old enough to be hit. [reverse-coded]	Male
Fathers'positive parenting and discipline behaviors	Proportion of fathers reporting use of positive parenting and discipline practices in the past three months. Questions include the following: whether the father said something nice about or praised the child; gave the child physical affection; went someplace or did something special with the child as a reward; showed or told the child that you love him/her. Discipline strategies include the following: taking away something the child liked; explaining why the child's behavior was wrong; redirecting (giving the child something else to do); asking the child to apologize	Male
Supportive environments for father engagement and positive parenting	Proportion of fathers agreeing or strongly agreeing that their social networks approve of engaging with children and using positive parenting skills. Items include the following: Your closest friends will tease you if you help your wife with child care. [reverse-coded]; Your father would admire you for telling stories to your child(ren).; You would be embarrassed if your mother saw your child(ren) misbehave and you did not discipline the child strongly. [reverse-coded]; Your friends think you should discipline your child(ren) with love.; Your respected community members will say you are not parenting your child well if—instead of beating your child—you try to explain to them their misbehavior. [reverse-coded]	Male
Father engagement in child health-promoting activities	Proportion of fathers and mothers reporting that the father took their child(ren) for rounds of immunization(s)	Male and Female
Knowledge of where to access family planning method(s)	Proportion of fathers and mothers who know where to obtain a method of family planning	Male and Female
Reduced unmet need for family planning	Proportion of fathers and mothers with unmet need for healthy timing and spacing of children. Assessed via those who are fecund and sexually active but are not using any method of contraception, and report not wanting any more children or wanting to delay the next child for 2 or more years	Male and Female

### Participant timeline {13}

This cRCT will roll out in a phased manner in conjunction with the larger implementation project using a subsample of individuals in three of the five implementation groups included as the intervention group in the trial. Sufficient time is planned to allow waitlist controls to transition to intervention groups in subsequent implementation rounds after they participate in the follow-up assessment. As shown in Table 6, for each trial cohort, baseline data collection will occur roughly one month before the start of a cohort, with endline data collection occurring roughly 8 months later (i.e., one month after the REAL Fathers intervention group ends). Follow-up data collection will occur 8 months after endline data collection.

**Table 6 Tab6:** Trial schedule: Enrolment, intervention, and assessments (adapted from SPIRIT 2013 Figure [36])

Date	Trial activity	Intervention activity		Cohort		
		REAL Fathers	Standard care	1	2	3
Nov 2023	Cohort 1 (C1) enrolment: eligibility screen and informed consent	Community engagement and sensitization (Steps 1–3)		1		
Dec 2023	C1 baseline assessment	REAL Fathers materials adaptations (Step 4) & Training of trainers (Step 5)		1		
Dec 2023 (after baseline)	Randomization (allocation to control or intervention)	Selection and training of mentors; selection of fathers (Steps 6–9)	x	1		
Jan–Aug 2024		Individual and group mentoring; community posters (Steps 10–11)	x	1		
Oct–Nov 2024	C1 endline assessment (1 mo. after intervention ends)			1		
Dec 2024–Jan 2025		Pause and Reflect				
Jan–Feb 2025	C2 enrolment: eligibility screen and informed consent	Community engagement and sensitization (Steps 1–3)			2	
Feb–Mar 2025	C2 baseline assessment	REAL Fathers materials adaptations (Step 4) & Training of trainers (Step 5)			2	
Mar 2025 (after baseline)	Randomization (allocation to control or intervention)	Selection and training of mentors; selection of fathers (Steps 6–9)	x		2	
Apr–Nov 2025		Individual and group mentoring; community posters (Steps 10–11)	x		2	
Jul 2025	C1 follow-up assessment			1	2	
Dec 2025	C2 endline assessment (1 mo. after intervention ends)				2	
Jan 2026	C3 enrolment: eligibility screen and informed consent	Community engagement and sensitization (Steps 1–3)				3
Feb 2026	C3 baseline assessment	REAL Fathers materials adaptations (Step 4) & Training of trainers (Step 5)				3
Feb 2026 (after baseline)	Randomization (allocation to control or intervention)	Selection and training of mentors; selection of fathers (Steps 6–9)	x			3
Mar–Oct 2026		Individual and group mentoring; community posters (Steps 10–11)	x			3
Aug 2026	C2 follow-up assessment				2	
Nov/Dec 2026	C3 endline assessment (1 mo. after intervention ends)					3
June 2027	C3 follow-up assessment					3

### Sample size {14}

Sample size is based on calculations using the outcome measure of proportion of young fathers who apply positive parenting behaviors. Based on the pilot studies on REAL Fathers intervention in Uganda, and to ensure sufficient statistical power of sub-group analyses at the regional level to obtain the largest sample size necessary, we assume only 40% of the young fathers use positive parenting skills at baseline [40]. From pilot studies, the REAL Fathers intervention should improve this proportion by at least 10% (effect size on absolute scale) by the endline [40]. The sample size computation is based on the formula:$$n=\frac{[2*{\left({Z}_{\alpha /4}+{Z}_{1-\beta }\right)}^{2}*\overline{P }(1-\overline{P })]}{{({P}_{1}-{P}_{0})}^{2}}\times Deff$$where:

*n* = minimum sample size of individuals required per arm of study

*Z*_α/4_ = the critical value of the standard normal variate at significance level of α/4 (*α* is assumed to be 0.05 or 95% certainty for improvement in the four primary outcome indicators). By setting the critical *Z* value corresponding to an alpha level of 0.0125 (i.e., α/4), our sample size calculation adjusts for multiple outcome testing while maintaining an overall 5% level of statistical significance for the trial.

*Z*_1-β_ = the critical value of the standard normal distribution at a power of 1-β (assumed to be 0.80 or 80% power)

*P*_0_ = the value of positive parenting indicator at the baseline; assumed 40%

*P*_1_ = the value of positive parenting indicator at the endline; assumed to be 50%—a 10-percentage point increase based on pilot studies$$\overline{P } = \frac{{P}_{1}+{P}_{0}}{2}$$

*Deff* = clustering effect, assumed to be 2.3

Based on the Uganda Bureau of Statistics 2019 population projections and Uganda Demographic and Health Survey 2016 data, only 4% of the male population (16–25 years) are young fathers who are married or cohabiting [6]. According to the latest Uganda population and housing census, the average village size is about 100 households [49]. Thus, no more than 10 young men (16–25 years) will be fathers whose eldest child is below the age of three years. To be on the conservative side, we assume that, on average, only 8 young fathers are eligible for the study from any given village. Let $$\overline{m }$$ denote this average and suppose *cv* is the coefficient of variation in the number of fathers across the different villages, and ρ is intra-cluster correlation (ICC). Pilot studies on the REAL Fathers intervention approximated ICC of 0.20–0.24 at the village level. Thus:$$Deff=\left(1+\left(\left({cv}^{2}+1\right)\overline{m }-1\right)\rho \right)=\left(1+\left(\left(0.063+1\right)\times 7-1\right)\right)\times 0.20=2.3$$

Based on the above parameters and an attrition rate of 10% between the baseline and endline, a total of 1872 couple dyads is required per study arm (3744 in total). This translates to 156 couples per district: 78 in each study arm from 6 villages; and 312 couples per geographical region. This makes an assumption of treatment effect size of 10% on indicators at project level and 80% statistical power and 95% certainty (alpha = 0.05).

The study is being conducted across regions characterized by diverse subcultures, both between and within locations. To ensure sufficient power to detect potential heterogeneity in treatment effects across key subcultural groups, we adjusted the sample size accordingly. Drawing on pilot data, we anticipate a moderate level of effect heterogeneity across these subcultures. According to Ford and Norrie (2016) [50] and Kent et al. (2018) [51], moderate heterogeneity corresponds to a coefficient of variation (CV) of approximately 20% in treatment effects. To account for this, we increased the originally planned sample size by 20%, resulting in a target of 2200 participants per study arm.

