### Trial design {8}

The impact of the REAL Fathers intervention will be assessed using a cluster-randomized controlled trial (cRCT) wait-list control rollout design [44]. This cRCT employs a superiority framework to test the null hypothesis that there will be similar differences in the primary and secondary outcomes from baseline to endline in both the REAL Fathers intervention group and the waitlisted control group receiving standard care [45]. The survey questionnaire will use validated questions, as piloted in a previous evaluation of the intervention [40], and will be extended to include items from Caregiver Reported Early Development Instruments (CREDI) [46] and socio-demographic items adapted to the local context. The phased rollout of the study will involve three cohorts, each with 1872 father-spouse dyads in the control group and 1,872 father-spouse dyads in the intervention group, for a total of 3744 father-spouse dyads across the three cohorts and study arms. Baseline data collection will occur roughly one month before the start of a cohort, with endline data collection occurring roughly 8 months later (i.e., one month after the 7-month mentoring period of the REAL Fathers intervention ends). Follow-up data collection will occur 8 months after endline data collection. This rollout design is optimal for resource constraint and ethical considerations. The trial is designed to match the speed of implementation, with a random sample of study participants in the intervention group selected from the overall implementation cohorts. Due to personnel and resource constraints in reaching the large number of program beneficiaries, staggered implementation of the intervention—and therefore also the cRCT trial which uses a sub-sample of program beneficiaries—is necessary. Further, from an ethical standpoint, in order to offer those in the control conditions of the study an opportunity to participate in REAL Fathers, several implementation cohorts are necessary, making this wait-list control rollout design the most appropriate for the study context.

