## Statistical methods

### Statistical methods for primary and secondary outcomes {20a}

The primary analysis will follow an intention-to-treat (ITT) approach, where all study participants will be analyzed according to their original randomization assignment at baseline. To evaluate intervention effects on primary and secondary outcomes, we will employ difference-in-differences (DID) regression models, which are well-suited for analyzing longitudinal data. DID estimation estimates the causal effect of the intervention by comparing changes in outcomes over time between the treatment and control groups while controlling for unobserved time-invariant characteristics, provided the parallel trends assumption and the Stable Unit Treatment Value Assumption (SUTVA) hold. To account for the complex survey design, we will incorporate random effects in the DID regression models to address clustering at the sub-county level (the unit of randomization). Additionally, clustered standard errors will be used to correct for within-individual autocorrelation and intra-cluster correlation (ICC) at the village level. Where necessary, sample survey weights will be applied to adjust for any imbalances in sub-county or district-level characteristics. As noted above in the “Sample size” section on sample size, we apply Bonferroni correction to account for multiple comparisons in primary outcomes while maintaining an overall 5% level of statistical significance for the trial.

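### The four primary outcomes are tested by single-step Bonferroni with sidedness unstated and an ambiguous Z(α/4); Holm on two-sided p-values keeps the 5% and never rejects fewer outcomes

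*Protocol article*

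**What the plan says.** The Sample size section {14} uses a normal critical value written Z with subscript α/4. It defines this as "the critical value of the standard normal variate at significance level of α/4", where α "is assumed to be 0.05 or 95% certainty for improvement in the four primary outcome indicators". It explains that by taking the "value corresponding to an alpha level of 0.0125 (i.e., α/4), our sample size calculation adjusts for multiple outcome testing", with the aim of "maintaining an overall 5% level of statistical significance for the trial". No numerical Z is printed.

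The section on statistical methods for primary and secondary outcomes {20a} carries this into the analysis: "we apply Bonferroni correction to account for multiple comparisons in primary outcomes while maintaining an overall 5% level of statistical significance for the trial". It refers back to the Sample size section and gives neither a Z cut-off nor a sidedness.

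On direction, Trial design {8} sets a superiority framework with a "null hypothesis that there will be similar differences in the primary and secondary outcomes from baseline to endline" in both arms. Objectives {7} hypothesises improvement in the intervention arm. The terms one-sided and two-sided appear nowhere in the article.

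**The concern.** A two-sided test at level α uses Z(α/2). Bonferroni over k two-sided tests uses Z(α/(2k)), so four tests need Z(α/8). Z(α/4) is the term for two two-sided tests, or for four one-sided ones. A reader who takes the symbol as an upper-tail quantile gets 2.241, and a reader who takes the words as a two-sided test at 0.0125 gets 2.498. An outcome with a two-sided p-value between 0.0125 and 0.025 could then be judged either way.

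Separately, the rule is single-step: every outcome must pass 0.0125, however strong the other three are. That is valid, but it gives up power that a step-down procedure recovers at the same overall 5% and with no added assumption. All four outcomes are of interest in their own right (partner violence, violent discipline, father-child engagement, child development), so the number of outcomes rejected matters.

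**Working it through.** **Inputs (Sample size {14}).** Overall α 0.05; four primary outcomes; α/4 = 0.0125; power 0.80 (Z = 0.8416); P0 = 0.40 and P1 = 0.50, so mean P = 0.45; Deff 2.3; attrition 10%; 1872 dyads per arm.

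**1. The two readings of the critical value.**
- Upper-tail area 0.0125: Z = 2.2414, equal to two-sided p = 0.025.
- Two-sided test at 0.0125 (tail 0.00625, that is α/8): Z = 2.4977.

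**2. Family-wise error over four independent tests.**
- One-sided at 2.2414: 1 − 0.9875⁴ = 4.9%.
- Two-sided at 2.2414: 1 − 0.975⁴ = 9.6% (Bonferroni bound 4 × 0.025 = 10%).
- Two-sided at 2.4977: 1 − 0.9875⁴ = 4.9% (bound 4 × 0.0125 = 5%).

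With a common correlation of 0.5 or 0.7 between test statistics (assumed; the documents give none), simulation gives about 8.3% and 7.0% for two-sided tests at 2.2414, and about 4.4% and 3.7% at 2.4977. Only the middle line exceeds 5%.

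**3. Does the sample size show which Z was used?** The printed formula is n = 2(Z + 0.8416)² × 0.45 × 0.55 / 0.10² × 2.3 = 113.85 × (Z + 0.8416)².
- Z = 2.2414: 113.85 × 3.0830² = 1082.1, so 1083; divided by 0.9, 1203 per arm.
- Z = 2.4977: 113.85 × 3.3393² = 1269.6, so 1270; divided by 0.9, 1411 per arm.

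Neither gives 1872. Solved backwards, 1872 × 0.9 = 1684.8 implies Z + 0.8416 = √(1684.8/113.85) = 3.847, so Z = 3.005, which matches no stated alpha. The sample size cannot settle the reading.

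**4. Power with 1872 per arm on the printed inputs.** Effective size per arm is 1872 × 0.9 / 2.3 = 732.5. The standard error is √(0.495/732.5) = 0.0260. The standardised effect is 0.10/0.0260 = 3.847.
- At 2.2414: Φ(3.847 − 2.241) = 94.6%.
- At 2.4977: Φ(3.847 − 2.498) = 91.1%.

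Both exceed the planned 80%.

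**5. Holm against single-step Bonferroni.** Holm orders the four p-values and compares the smallest with 0.05/4 = 0.0125, then 0.05/3 = 0.0167, 0.05/2 = 0.025 and 0.05, stopping at the first failure. The first step is the Bonferroni threshold and the later ones are larger, so every outcome rejected by Bonferroni is rejected by Holm. The overall 5% holds under any dependence between outcomes.

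The simulation used two-sided tests, with all four outcomes truly affected and each having 80% power under Bonferroni (an assumption for illustration):

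| Correlation | Mean power, Bonferroni | Mean power, Holm | All four rejected, Bonferroni | All four rejected, Holm |
|---|---|---|---|---|
| 0 | 0.80 | 0.89 | 0.41 | 0.69 |
| 0.5 | 0.80 | 0.87 | 0.56 | 0.76 |
| 0.7 | 0.80 | 0.87 | 0.62 | 0.79 |

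The independent Bonferroni entry checks by hand: 0.8⁴ = 0.41.

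**The case against.** The strongest reply is that nothing is broken. Z(α/4) is an input to the sample size. The decision rule is Bonferroni over four outcomes at an overall 5%, so p < 0.0125 each, and that controls the error with either one-sided or two-sided p-values. The words defining Z fit a two-sided test at 0.0125 as well as a one-sided one. Sidedness is a detail that an article often leaves to the analysis plan. All of this stands.

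A reader might go further and infer that the plan states a two-sided null, prints a cut-off of 2.241, and therefore runs at a family-wise error near 10%. The documents do not support that. The null of similar changes fits either alternative, the hypothesis is worded as improvement, no numerical Z appears, and no section sets a two-sided threshold of 0.025. Nor can one infer that harm goes untested, since no section says the tests are one-sided.

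It can also be said that Holm is a preference, because Bonferroni is valid. That is true as far as error control goes. But Holm dominates Bonferroni in the number of outcomes rejected, at the same error rate and with no further assumption, so it is worth proposing as an improvement and not as the correction of an error.

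**Conclusion.** The point holds as a notational ambiguity together with a cheap improvement in method. The symbol Z(α/4) and the missing sidedness allow cut-offs of 2.241 or 2.498. A breach of 5% would arise only if two-sided results were judged against 2.241 (9.6% if the tests are independent), and the plan does not say that they will be. Read as two-sided p < 0.0125, the rule keeps the 5%, and power is about 91% on the printed inputs, so the sample size is not at risk from this point.

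The gain from Holm depends on how many outcomes are truly affected and on their correlation. In the case computed above, mean power rises by about 7 to 9 percentage points, and the chance of rejecting all four by about 17 to 28 points. These figures assume one test per primary outcome, equal power and a common correlation. That Holm never rejects fewer outcomes needs none of these assumptions.

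**What to change.** In the statistical methods section {20a}, replace single-step Bonferroni by Holm's step-down on the two-sided p-values of the four primary outcomes, with thresholds 0.0125, 0.0167, 0.025 and 0.05 and an overall two-sided 5%. In the Sample size section {14}, write the term as Z(α/8) = 2.498 (two-sided 0.0125). Date the change before the final analysis of the full dataset.

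The cost is wording only, and this point calls for no more participants. The one drawback is that simultaneous intervals matching Holm are less simple. The 98.75% Bonferroni intervals can still be shown, with a note that an outcome rejected at a later Holm step may have a 98.75% interval that includes no effect.

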**Methods:**

To assess the REAL Fathers intervention, we use a cluster-randomized controlled trial design within 48 sub-counties randomly sampled from 24 districts in six regions of Uganda. Sub-counties were randomly allocated to treatment or control arms at baseline. Study participants are fathers ages 16–25 years and their cohabitating wives whose eldest child is below the age of 3 years (*n* = 3744 couple dyads). Primary outcomes are the following: (1) reduced intimate partner violence; (2) reduced violent discipline of children; (3) increased father-child engagement and play; (4) improved early childhood development. Secondary outcomes include the following: (1) father’s knowledge of and (2) attitudes towards positive parenting and discipline; (3) father’s use of positive parenting and discipline; (4) father’s use of emotional engagement with child; (5) couple communication and conflict resolution; (6) gender equitable household and caregiving decision-making and behaviors; (7) father engagement in child health-promoting activities; (8) improved knowledge of family planning methods; (9) reduced unmet need for family planning; (10) reduced problem alcohol use; and (11) supportive community norms for father-child engagement and play. Longitudinal survey data will be collected by trained enumerators using KoboCollect in six local languages at three time points: one month before the intervention (baseline); one month after the intervention (endline); and nine months after the intervention (follow-up). Intervention effects on primary and secondary outcomes will be assessed using difference-in-differences (DiD) mixed-effects models that account for the clustered design.

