## Interventions

### Explanation for the choice of comparators {6b}

Random allocation is made between intervention and wait-list control groups, as randomized at the sub-county level. The intervention group will receive the REAL Fathers intervention within a month after the screening process, while the wait-list control group will receive the REAL Fathers intervention after follow-up data collection (wave three) is conducted. Participants in the control group will continue to access standard care and services that are already available in their communities. These include the following: village health team visits and referrals to clinics when applicable; early childhood development centers and programming; family planning and social-economic interventions from Government, as described in further detail in the “Plans to promote participant retention and complete follow-up” section below.

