## Assignment of interventions: allocation

### Sequence generation {16a}

The study will be implemented in 24 districts in six geographical regions of Uganda. As noted above, in each district, a simple random sample of two sub-counties will be taken. These sub-counties will be randomly allocated to either the treatment or control condition (1:1 within each district) using the Mersenne Twister algorithm via the RAND function in Microsoft Excel [52]. For subsequent follow-up studies (midline and endline), all enrolled participants will be re-interviewed at midline and endline surveys. (See Table 7 for sample randomization of sub-counties data).

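### The sample size takes its design effect from villages although sub-counties are randomised, so the stated 80% power is not justified for this design

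*Protocol article*

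**What the plan says.** The unit of randomisation is clear. Explanation for the choice of comparators {6b}: "Random allocation is made between intervention and wait-list control groups, as randomized at the sub-county level". The abstract places the trial "within 48 sub-counties randomly sampled from 24 districts in six regions of Uganda", and Sequence generation {16a} allocates the two sub-counties of each district 1:1. Statistical methods {20a} uses random effects to "address clustering at the sub-county level (the unit of randomization").

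Sample size {14} works at another level. It says "Pilot studies on the REAL Fathers intervention approximated ICC of 0.20–0.24 at the village level" and uses 0.20. It assumes that "only 8 young fathers are eligible for the study from any given village", puts 7 into the formula, and reaches a design effect of 2.3. No sub-county ICC appears.

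The target is a rise from 40% to 50% with 80% power, with a critical value "corresponding to an alpha level of 0.0125 (i.e., α/4"). Whether the test is one- or two-sided is not stated. With 10% attrition the section arrives at 1,872 couples per arm, that is 78 per arm in each district, drawn from six villages. A later paragraph raises the target to 2,200 per arm for effect heterogeneity, while Recruitment {15} keeps 1,872.

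On the outcome: "Sample size is based on calculations using the outcome measure of proportion of young fathers who apply positive parenting behaviors". Table 5 lists positive parenting behaviours as a secondary outcome.

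**The concern.** In a cluster trial the design effect has to reflect the correlation among all members of a randomised cluster. Here that cluster is a sub-county of 78 couples spread over several villages. A village-based design effect is complete only if couples in different villages of the same sub-county are uncorrelated. The plan's own model gives sub-counties a random effect, so it does not assume this.

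With 78 couples per cluster, even a small sub-county correlation adds noticeably to the variance. If the 80% figure has no basis at the randomised level, a null result on partner violence or child development cannot be judged against it. The calculation is also a single-time comparison of a secondary outcome, whereas the analysis is a difference-in-differences on four other outcomes.

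**Working it through.** **1. The plan's design effect.** Deff = 1 + ((cv² + 1)m − 1)ρ, with cv² = 0.063, m = 7, ρ = 0.20:
1 + (1.063 × 7 − 1) × 0.20 = 2.288, which matches 2.3. (With the brackets as printed the result would be 1.49; this looks like a typesetting slip.)

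**2. The plan's sample size.** n = 2(Z + 0.8416)² × 0.45 × 0.55 / 0.10² × Deff, divided by 0.9 for attrition.
- Two-sided 0.0125 (Z = 2.498): 552.0 × 2.3 / 0.9 = 1,411 per arm.
- One-sided 0.0125 (Z = 2.241): 470.5 × 2.3 / 0.9 = 1,202 per arm.

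Neither gives 1,872. With 1,872 × 0.9 = 1,685 evaluable per arm, Deff 2.3 gives 91% power (two-sided), so the number carries unexplained slack.

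**3. Adding the sub-county level.** Let ρs be the correlation between couples in different villages of one sub-county. The protocol gives no value, so ρs is an assumption shown as a range. Evaluable couples per sub-county: M = 1,684.8 / 24 = 70.2. Then
Deff = 2.288 + (70.2 − 7.441)ρs; SE = √(0.495 × Deff / 1,684.8); power = Φ(0.10/SE − Z).

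| ρs | Deff | Two-sided 0.0125 | Same, t on 46 df | One-sided 0.0125 |
|---|---|---|---|---|
| 0 | 2.29 | 91% | 89% | 95% |
| 0.01 | 2.92 | 82% | 79% | 88% |
| 0.02 | 3.54 | 73% | 69% | 80% |
| 0.05 | 5.43 | 50% | 47% | 60% |

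Break-even for 80% power:
- Two-sided: the largest Deff is 1,684.8 / 552.0 = 3.05, so ρs = (3.05 − 2.288) / 62.76 = 0.012.
- One-sided: the largest Deff is 1,684.8 / 470.5 = 3.58, so ρs is about 0.02.
- At 2,200 per arm, two-sided: ρs is about 0.017.

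**4. The planned difference-in-differences.** Take cluster autocorrelation c, individual correlation r = 0.3 and about 10 villages per sub-county (70.2 / 7); c and r are assumptions. In units of P̄(1 − P̄), the variance of a cluster's change is
V = 2[ρs(1 − c) + (0.20 − ρs) × 1.063(1 − c)/10 + 0.80(1 − r)/70.2], and SE = √(0.495 × V / 24).
Example: ρs = 0.05 and c = 0.8 give V = 0.0423 and SE = 0.0295.

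Power, two-sided 0.0125, t on 46 df:

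| ρs | c = 0.8 | c = 0.5 |
|---|---|---|
| 0.01 | 94% | 74% |
| 0.02 | 90% | 64% |
| 0.05 | 78% | 44% |

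**5. Village size.** The document implies four values:
- 8 eligible per village in the text;
- 7 in the formula;
- 78 / 6 = 13 from the couples and villages per arm in each district (Sample size {14});
- 156 / 24 = 6.5 from the 24 villages per district (Recruitment {15}).

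With 13, Deff = 1 + (1.063 × 13 − 1) × 0.20 = 3.56. Two-sided power is then about 72% before any sub-county correlation is added.

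**The case against.** Four points count on the other side.

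- **The planned analysis is not the printed formula.** A reader might infer that 80% power holds only if sub-county clustering is near zero. That is true of the post-only formula. A difference-in-differences on the same couples removes stable sub-county differences, and with allocation within districts only the correlation left within a district matters. Step 4 shows 94% and 90% at ρs of 0.01 and 0.02 when autocorrelation is 0.8. This stands against the stronger reading. It does not rescue the stated figure, because the result turns on correlations that the protocol does not state.
- **There is slack.** 1,872 exceeds what the inputs require. A reader might take the use of m = 7 rather than 8, and of the low end of the ICC range, as fatal. It is not: m = 8 gives Deff 2.50 and 88% power, and m = 8 with ICC 0.24 gives Deff 2.80 and 84% (two-sided, no sub-county correlation). The slack is unexplained, however, and on the post-only formula with the plan's own m and ICC it is used up at ρs of about 0.012.
- **The input is near the worst case.** P̄(1 − P̄) is 0.2475 against a maximum of 0.25, and α/4 allows for four primary outcomes. A binary primary outcome with the same 10-point effect and the same clustering would have about this power or more. That does not cover a different effect or ICC, or the CREDI measure, which Table 4 defines as scores.
- **The analysis handles the clustering.** A reader might infer that the primary test is invalid. The sub-county random effect in {20a} means that this error does not reach it.

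**Conclusion.** The point holds as a failure to justify power at the randomised level. The design effect of 2.3 omits one level of correlation, and the 80% claim does not follow from the stated inputs in either direction: they need about 1,400 per arm two-sided, and they ignore sub-county clustering.

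On the plan's own formula, power at 1,872 per arm runs from 91% at ρs = 0 to 50% at ρs = 0.05 (two-sided). For the planned analysis it runs from 94% to 44% over the assumed ranges. These ranges rest on assumed sub-county ICCs, autocorrelations of 0.5 and 0.8 and an individual correlation of 0.3; none is in the document. They do not show that the trial is underpowered. They show that the document cannot tell the reader whether it is.

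The conflict over village size (13 against 6.5 to 8) matters more than the choice between 7 and 8. The lack of any assumed effect or ICC for a primary outcome matters most for CREDI.

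**What to change.** Leave enrolment as it is and restate the calculation:

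- Use a three-level design effect (couple, village, sub-county), 24 clusters per arm with t degrees of freedom, and the village size actually sampled.
- State whether the 0.0125 level is one- or two-sided.
- Base power on the planned difference-in-differences estimator. Take village and sub-county ICCs from Cohort 1 baseline data pooled over arms, and show a range for the cluster autocorrelation.
- Reconcile 1,872 with its inputs and with the 2,200 target (20% on 1,872 would be 2,246), and reconcile the villages per sub-county between {14} and {15}.
- Give power or the detectable effect for each of the four primary outcomes, with CREDI on its own scale.

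The cost is a few hours of calculation on data already collected and a revised paragraph. The restated power may be less favourable than 80%.
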